## Methods and analysis

To address the study objectives, we will conduct a three-arm (1:1:1), parallel groups, RCT. The study received ethical approval from the Swedish Ethical Review Authority (16 April 2024, Dnr 2024-01630-01) and was prospectively registered in the ISRCTN trial registry on 12 June 2024 (ISRCTN87600318). This protocol has been written following Standard Protocol Items: Recommendations for Interventional Trials (SPIRIT) guidelines.^49^ Recruitment started in February 2025 and is planned to not extend beyond February 2026.

### Study setting, recruitment and eligibility criteria

Through social media (Meta-platform, including Facebook and Instagram) and web search engine (Google search) advertisements, we will target individuals in the general population of Sweden looking for help online to reduce their drinking. We will target keywords that relate to reducing alcohol consumption, such as ‘drinking less’, ‘how to reduce my drinking’, ‘cutting down on alcohol’. Individuals will show interest in the study by sending a text message to a dedicated phone number. They will immediately receive a response with a link to a web page presenting informed consent materials (see online supplemental Appendix A). To keep participants blinded to avoid research participation effects,^50^ we will frame the study as one in which digital materials designed to help individuals reduce their drinking are evaluated, but details of the interventions will not be disclosed. This raises ethical issues, as the control group will not immediately receive an evidence-based intervention but only digital information about alcohol and health. Instead, control group participants will, at the end of trial participation, receive the personalised intervention.^16^

Consenting participants will be asked to respond to a baseline questionnaire, which will also assess eligibility (see online supplemental Appendix B for the questionnaires used in the study). Individuals will be eligible to participate if they are aged 18 or older, have access to a mobile phone and are classified as drinking at risky levels according to current Swedish guidelines. Since this is an effectiveness trial, we will not exclude participants based on concomitant care or restrict the use of other support. Immediately after completing the baseline questionnaire, eligible participants will be randomly allocated to one of the three study groups.

### Interventions

#### Control group

Participants allocated to online support materials will be referred to two national websites with information about alcohol and health (ie, 1177.se and IQ.se). They will be instructed to read these materials and use any available support. They will also be informed that we will contact them again to conduct follow-up surveys. At the end of trial participation, 8 months postrandomisation, control group participants will receive the personalised intervention which has been shown to be effective.^16^

#### Personalised intervention group

Participants allocated to the personalised intervention will be given immediate access to a digital alcohol intervention for 16 weeks which provides personalised feedback based on the individual’s current consumption in contrast to national guidelines and compared with average consumption levels in the same sex and age group. Notably, this intervention is not tailored for drinking motives or readiness to change, but based on social cognitive theories of health behaviour.^51^ The digital alcohol intervention targets improving motivation and self-efficacy, as well as teaching new skills and addressing environmental constraints—which are understood to improve the likelihood of successful behaviour change,^52^ including for changing one’s drinking.

The core element of the intervention is a text message sent each Sunday afternoon acting as a proactive reminder to engage in the intervention materials. The message includes a prompt to self-monitor current alcohol consumption and a link to a web-based screening tool. The screening tool assesses the past week’s consumption, and participants are subsequently given access to a toolbox with modules containing advice for behaviour change. The content of these modules is anchored in state-of-the-art empirical evidence for which active ingredients are effective for supporting reduced alcohol consumption, including behaviour substitution, problem-solving, goal setting, review of behavioural goals, self-monitoring, normative feedback and understanding the consequences of alcohol consumption.^53 54^

#### Enhanced tailored intervention group

Participants allocated to the enhanced tailored intervention group will for 16 weeks receive an intervention that follows the same logic as the personalised intervention. The key difference between the two is that after the weekly self-monitoring and feedback on current consumption, participants will be given tailored exercises and advice for behaviour change which have been selected based on the participant’s drinking motives and readiness to change. Periodically, participants in the tailored intervention group will be asked to reassess their readiness to change and motives, using the readiness to change questionnaire (treatment version)^55 56^ and the drinking motives questionnaire (short form).^57^ Matching will be based on the latest available data for participants concerning motives for drinking and readiness to change. Participants who have not progressed to the action stage after 8 weeks will nonetheless receive content related to the action category of readiness to change for the following 4 weeks. The rationale for this is that if no progress has been produced from the precontemplation and contemplation content, then providing something new may be more appropriate. Notable is that the precontemplation and contemplation materials are still available. Weeks 13 through 16 are then again tailored to readiness to change. Online supplemental Appendix C contains details of the enhanced tailored intervention and the reassessment schedule.

### Outcomes

For primary and secondary outcomes, we will use the international consensus-driven core outcome set for brief alcohol interventions,^18^ measured using the recommended questionnaire items.^58^ All questionnaires will be completed by participants on their mobile phones and initiated by sending a text message with a link to the questionnaires (see online supplemental Appendix B for all questionnaires used).

#### Primary

Past week’s alcohol consumption: measured by asking the number of standard drinks consumed each day of the past week (which are then summed).Frequency of heavy episodic drinking in the past month: measured by asking about the number of episodes of heavy drinking in the past month (four or more standard drinks).

#### Secondary

Secondary outcomes are asked in reference to the past 3 months:

Frequency of drinking: measured using the first item of the Alcohol Use Disorders Identification Test-Consumption (AUDIT-C).^59^Typical number of drinks consumed on a drinking day: measured using the second item of the AUDIT-C.^59^Frequency of drinking six or more drinks: measured using the third item of the AUDIT-C.^59^Combined consumption measure: measured using the total score of AUDIT-C.^59^Hazardous and risky drinking: measured using cut-off points of >3/4 (woman/man) points on the AUDIT-C scale.^60^Alcohol-related consequences: measured by asking the 15-item Short Inventory of Problems questionnaire (SIP).^61 62^Alcohol-related injury: a single item**,** based on the SIP questionnaire**,** concerning injuries inflicted while drinking or being intoxicated.Use of emergency healthcare services: a single item concerning the number of visits to emergency healthcare services adapted from EconForm90.^63^Quality of life: measured using the Patient-Reported Outcomes Measurement Information System (PROMIS) Global Health 1.2 items, a 10-item questionnaire with higher scores indicating higher quality of life.^64^

#### Mediators

Confidence: in one’s ability to reduce drinking.Knowledge: of how to reduce one’s drinking.Injunctive norms: peer’s approval of drinking.Descriptive norms: perceptions about other’s drinking.

### Participant timeline

In figure 1, a SPIRIT figure depicts the trial timeline. At 2 and 4 months postrandomisation, primary and mediator outcomes will be assessed to estimate the effects of immediate exposure and prolonged exposure to the interventions. The 4-month follow-up will also include a user evaluation questionnaire. At 8 months postrandomisation, all outcomes will be measured to estimate the persistent effects of the interventions. Up to three reminder texts will be sent at each follow-up interval, followed by phone calls to collect data from those not responding (maximum of five attempts).

**Figure 1 F1:**
[figure not shown]
SPIRIT figure representing participants’ timeline throughout the trial. SPIRIT, Standard Protocol Items: Recommendations for Interventional Trials.

### Sample size

This trial will use a Bayesian sequential design to avoid under-recruitment and over-recruitment.^65^,^68^ Bayesian sequential designs use target criteria which are evaluated continuously as data are made available, and recruitment ends once the criteria are considered sufficiently fulfilled. Throughout the study period, we will model the primary outcomes according to the analysis plan, and regression coefficients representing the effect of allocation to enhanced tailored versus personalised intervention at the 4-month interval will be asserted against target criteria for benefit, harm and futility. Note that relative differences between groups are estimated as incidence rate ratios for primary outcomes. We will aim to have one criterion fulfilled per primary outcome measure. In the case of futility, two additional criteria will be considered where intervention groups are combined and contrasted against the control group. The criteria for ending recruitment are:

Weekly alcohol consumption benefit/harm: the posterior probability is greater than 95% that past week’s alcohol consumption is *less/greater* in the enhanced tailored intervention group versus the personalised intervention group.

Frequency of heavy episodic drinking benefit/harm: the posterior probability is greater than 95% that the number of episodes of heavy drinking is *fewer/more* in the enhanced tailored intervention group versus the personalised intervention group.

Weekly alcohol consumption futility: the posterior probability is greater than 95% that the relative difference in past week’s alcohol consumption between the enhanced tailored intervention group versus the personalised intervention group is less than 15%.

Frequency of heavy episodic drinking futility: the posterior probability is greater than 95% that the relative difference in the number of episodes of heavy drinking between the enhanced tailored intervention group and the personalised intervention group is less than 15%.

In case of futility—benefit/harm versus controls: the posterior probability is greater than 95% that past week’s alcohol consumption is *less/greater* and number of episodes of heavy drinking are *fewer/more* in the intervention groups combined versus controls.

In case of futility—futility versus controls: the posterior probability is greater than 95% that the relative difference in both primary outcome measures between the combined intervention groups and the controls is less than 15%.

While the final sample size is not determined a-priori in Bayesian group sequential designs, we conducted a series of simulations with effect sizes of 15% weekly alcohol consumption difference. The code for the simulations can be found in online supplemental Appendix D. Simulations suggested that approximately 1750–2200 participants will be necessary to recruit. Since this is an online trial of digital interventions, we require minimal resources per recruited participant; thus, resources are available even if the sample size required is larger than anticipated.

There are a few considerations on the above design: first, the criteria added if the primary contrast is found futile will be used to decide when to stop recruiting in case the available evidence suggests that the contrast against controls is worth considering further. The rationale for this is due to this trial employing a longer follow-up interval (8 months) than our previous trial of the personalised intervention (which stopped at 4 months), and the current trial attempting to blind participants; thus, evidence gaps can be addressed by continuing recruitment in this case. Second, by using Student’s t priors centred at the null, estimates will be pulled towards the null when data is scarce, protecting against spurious and potentially erroneous findings.^68^ Third, due to the nature of Bayesian inference, there is no need to adjust analyses for multiple looks at the data.^69^ Fourth, since no sample size is prespecified, we reduce the risk of stopping recruitment both too early and too late,^65 68 70^ while also allowing the trial to be stopped if the intervention is deemed harmful. Finally, from previous and ongoing trials using online recruitment with this type of design,^16 71 72^ we anticipate that recruitment will not last for more than 12 months.

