#### Models for primary and secondary outcomes

Primary outcomes will be modelled using multilevel regression with participant-level adaptive intercepts and group-by-time interactions (2-month, 4-month and 8-month follow-up measures). Secondary outcomes are measured at 8 months only and will be analysed using regression models with a group covariate. Both primary alcohol consumption outcomes will be modelled using negative binomial regression, and so will the number of visits to emergency healthcare services. Logistic regression will be used for hazardous and risky alcohol consumption classification, and linear regression will be used for the combined consumption measure (AUDIT-C), alcohol-related consequences scores (SIP) and quality of life (PROMIS Global Health 1.2). Frequency of drinking, typical number of drinks consumed on a drinking day and alcohol-related injury will be modelled using ordinal regression. Models of primary outcomes will be adjusted for baseline measures of the outcome using a time-by-baseline interaction, and models of secondary outcomes will be adjusted for baseline measures of both primary outcomes. In addition, all models will be adjusted for age, sex, education and access to money on short notice (see online supplemental Appendix A). We will use Student’s t priors for the main intercepts and coefficients, and half-Student’s t priors for dispersion and error terms. All Student’s t priors will be centred at 0, have a scale of 2.5 and 3 df. We will use normal priors for adaptive intercepts with standard normal hyperpriors for the SD parameters (mean=0, SD=1).

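### The prior fixed for the group effects is practically flat for effects near 15%, so it does not give the protection against spurious findings that the protocol claims for it

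*Protocol article*

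**What the plan says.** The Sample size section of the protocol article describes criteria that are "evaluated continuously as data are made available, and recruitment ends once the criteria are considered sufficiently fulfilled". The benefit and harm criteria each need a posterior probability above 95% for the 4-month contrast of enhanced tailored against personalised intervention. The futility criterion needs the same probability that the relative difference is under 15%. One criterion should be met for each of the two primary outcomes.

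The same section lists points in the design's favour. The second is the null-centred prior: "estimates will be pulled towards the null when data is scarce, protecting against spurious and potentially erroneous findings". The third is separate: "due to the nature of Bayesian inference, there is no need to adjust analyses for multiple looks at the data".

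The section on models for primary and secondary outcomes fixes the prior. "We will use Student’s t priors for the main intercepts and coefficients", and "All Student’s t priors will be centred at 0, have a scale of 2.5 and 3 df". The scale on which it acts is also settled: "Both primary alcohol consumption outcomes will be modelled using negative binomial regression", and in the Sample size section "relative differences between groups are estimated as incidence rate ratios for primary outcomes". So the prior sits on log rate ratios. The article gives no tighter prior for the treatment contrasts.

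**The concern.** A null-centred prior protects against chance findings in small samples only if it is narrow relative to the effects under study. On a log-rate scale an effect of 15% is a coefficient of about −0.16, and a prior with scale 2.5 is some fifteen times wider than that. The prior and the claim are both printed in the article, so this is a stated safeguard that can be checked directly.

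At stake is how a stop is read. If the prior adds nothing, the benefit and harm rule works like repeated one-sided 5% tests in each direction on unshrunk estimates, and a reader told that the prior guards against early chance results would trust an early stop too much. The simulations that the article describes use a 15% difference, and it reports no rate of false benefit or harm under no difference.

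**Working it through.** **The plan's own figure.** The article expects 1750–2200 participants. A fixed-sample check on the log scale (one-sided 5%, 80% power, assumed SD 1.0) gives 2 × 1.0² × (1.645 + 0.842)² / (ln 0.85)² = 12.37 / 0.0264, or about 469 per arm and 1407 over three arms. With 20% loss this is 1407 / 0.8 ≈ 1759; with SD 1.25 and no loss it is 2196. The stated range is attainable. It cannot be reproduced, because its inputs are in Appendix D, which is not shown. Nothing here says that it is wrong.

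**Inputs from the article.** Student's t prior, centre 0, scale 2.5, 3 df; log-IRR coefficients; 95% threshold in each direction; 15% margin.

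**1. Width of the prior.**
- 95% range: exp(±2.5 × 3.182) = exp(±7.956), so IRR 0.00035 to 2853.
- Mass on IRR 0.85–1.15: density at zero 0.3676 / 2.5 = 0.147, times width ln 1.15 − ln 0.85 = 0.302, gives 0.044, or 4.4%.
- Mass on IRR 0.5–2: 20%, so 80% lies outside.

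**2. Shrinkage of an observed IRR of 0.70.** With a normal likelihood the shift is about SE² × 4|x| / (3 × 2.5² + x²), with x = ln 0.70 = −0.357. The second factor is 1.427 / 18.88 = 0.0756.

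| SE | Shift in log IRR | Estimate after shrinkage |
|---|---|---|
| 0.1 | 0.0008 | 0.7005 |
| 0.2 | 0.0030 | 0.702 |
| 0.3 | 0.0068 | 0.705 |

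At SD 1.0, SE = √(2/n), so SE 0.2 corresponds to n = 50 per arm. Shrinkage on the log scale is 4.0% at 10 per arm, 0.9% at 50 and 0.05% at 600.

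**3. Evidence needed to cross 95%.** Near zero the prior has precision (4/3) / 2.5² = 0.213. The required z is about 1.645 × √(1 + 0.213 × SE²). At 50 per arm this is 1.645 × √1.0085 = 1.652, against 1.645 with a flat prior.

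**4. Null crossings, one outcome, benefit or harm.** Simulated at IRR 1.0 with assumed SD 1.0, at most 733 per arm, and 4-month data available at once:

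| Looks (per arm) | Flat prior | Protocol's t prior | Normal(0, 0.2) |
|---|---|---|---|
| every participant from 10 | 66.4% | 65.8% | 40.4% |
| every participant from 20 | 61.9% | 61.6% | 41.0% |
| every 10 from 20 | 53.6% | 53.4% | 35.1% |
| every 25 from 50 | 42.8% | 42.7% | 30.6% |
| every 100 | 29.5% | 29.4% | 22.7% |

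Counting only crossings by 100 per arm, where data are scarcest, the largest gap between flat and t is 46.3% against 45.4%. The prior removes at most about 1 percentage point.

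**5. The joint rule, with the follow-up lag.** Recruiting 1750–2200 over 12 months puts 4/12 of them, 583–733 in all or 194–244 per arm, inside the 4-month window at a stop, before attrition. A simulation with a flat prior (indistinguishable from the t prior by step 4), SD 1.0, outcome correlation 0.6, looks every 20 per arm from 50 to 700, and 200 per arm added after the stop gives:

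| Quantity | At the stop | Final analysis |
|---|---|---|
| Null: benefit or harm on at least one outcome | about 35% | about 19–20% |
| Null: benefit or harm on weekly consumption | 26–27% | 12% |
| True IRR 0.85: median weekly estimate among benefit stops | 0.81 | 0.84 |

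A single fixed look at one outcome would give 10%, being 5% in each direction. SDs of 0.9 and 1.1 give similar final results (18–20%, 11–12% and 0.84).

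**The case against.** Four points on the other side have force.

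*The criteria end recruitment, not the trial.* Follow-up runs to 8 months, and the Ethics and dissemination section places the analysis after the complete data set is available. A reader might infer that a third of null trials would report a false effect, or that the published effect would be markedly exaggerated. The documents do not support this: the estimate at the stop is not the reported result, and the added follow-up brings both figures well down. What stands is a residual excess, which grows if attrition shrinks the group still in follow-up.

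*The unadjusted looks do not rest on the prior.* A reader might infer that the prior is the reason for making no adjustment. The article lists the two as separate points and bases the second on the nature of Bayesian inference. The concern is therefore confined to the protection claim.

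*Shrinkage is not zero, and the claim is limited to scarce data.* True: it reaches about 4% at 10 per arm. Even there the effect on false crossings is under 1 percentage point. It is also tempting to say that no minimum first look exists. The article states none, but Appendix D may.

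*The prior is not the main driver.* Even Normal(0, 0.2) leaves sizeable null rates in step 4, because the 95% threshold and the frequency of looks matter more. A particular sceptical prior is also a choice, and the design commits to posterior probabilities rather than type I error. This limits what a new prior can achieve. It does not make the printed claim correct.

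**Conclusion.** The concern holds as a mismatch between a stated property and the prior that is meant to supply it. That part follows from the article's own figures: 4.4% of prior mass on IRR 0.85–1.15, an observed 0.70 moved to 0.702 at SE 0.2, and a required z of 1.652 instead of 1.645 at 50 per arm.

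The consequence is moderate and rests on assumptions: log-scale SD about 1.0, outcome correlation 0.6, a normal approximation to the likelihood, the look schedule, and 200 per arm in follow-up at the stop. On those, about 35% of null trials meet a benefit or harm criterion on at least one outcome at the stop, and about 19–20% show one at final analysis. The rates at the stop vary widely with the look schedule. Exaggeration largely disappears by final analysis.

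**What to change.** 1. Run the Appendix D simulations at a true IRR of 1.0, with the planned looks, the rule requiring one criterion per outcome, and the 4-month lag. State the false benefit and harm rates at the stop and at final analysis.
2. Then take one of two routes. Either delete the statement that the prior protects against spurious findings, or make it true by giving the group contrasts used for stopping a sceptical prior on the log-IRR scale. One example is Normal(0, 0.2), whose 95% range is exp(±1.96 × 0.2) = 0.68 to 1.48. Scale 2.5 can stay for intercepts and nuisance covariates.
3. Because recruitment began in February 2025, report any change of prior as a deviation, which the article already undertakes to do.

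The first route costs a simulation run and a sentence. The sceptical prior costs roughly 9–15% more evaluable participants on average under a true 15% effect, with looks up to 700 per arm. With the ceiling raised to 2000 per arm, the simulated mean total rose from 791 to 931 (18%) at SD 1.0 and from 1156 to 1406 (22%) at SD 1.25. The article says that resources are available for a larger sample.
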